### Study assessments

2.7

Assessments are performed at baseline, intervention completion (3 months), and 6 months since baseline (see Table 1). Visits take between 2 and 3 hours to complete and include the completion of study questionnaires, the 6-minute walk test, direct measurements of hip and waist circumference, height, weight, and accelerometer fitting.

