### Statistical analyses

2.8

Our choice of sample size (n = 40, 10 participants per condition) was determined by the scope and timeline of this project. Given that this is a proof of concept study, our focus is not on strict hypothesis testing but rather on estimates of effect size and corresponding confidence intervals.

Depending upon variable characteristics (categorical or continuous), Fisher exact test or *t* tests will be used to compare participants at baseline on socio-demographic and medical characteristics. Baseline characteristics not balanced by randomization, as well as variables associated with the study outcomes, will be included as covariates in linear or logistic regression analyses.^[58,59]^

Rates of retention and attendance, as well as program satisfaction scores at 3 and 6 months will be calculated separately for each of the 4 groups. The study will be considered feasible if retention rates of at least 80% are achieved, if participants attend at least 70% of the planned sessions, and if they report completion of at least 70% of the assigned individual home practice exercises. For acceptability, each intervention will be considered acceptable if at least 80% of participants indicate grade 4 enjoyment ratings on a visual scale ranging from 0 to 4.

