To determine effect sizes on cognitive function, the ZAVEN^[47]^ composite cognitive score will be calculated for each participant by converting Digital Symbol Substitution Test, F-A-S verbal fluency test, and International Shopping List Test scores to standardized z-scores. The effects of group on ZAVEN scores at 3 and 6 month follow-ups will be estimated using a series of mixed effects longitudinal models controlling for baseline. Models will include a subject-specific intercept to adjust for repeated measures of the outcome over time within participant. A single model will allow for all pairwise comparisons between groups (MT + AT vs MT alone, vs AT alone, vs neither) with the goal of estimating effect sizes and corresponding confidence intervals. A similar approach will be used to assess effects of intervention on each measure of working memory (Groton Maze Learning Test; One-Card Learning Task; and One-Back Test). Last, exploratory mediation analyses will be conducted to assess associations between changes in fitness and other mediators at 3 months with changes in cognitive score at 6 months. As sample size is limited for mediation models, our interest in is estimating effect sizes for both the *a* path (group effects on mediators at 3 months) and *b* path (mediators at 3 months on ZAVEN scores at 6 months), using a similar set of mixed effects models as described previously.

To account for missing data, analyses will be performed according to the intention-to-treat approach.^[60]^ If participants withdraw from the intervention they are asked to complete follow-up assessments. If substantial missing data are encountered, possible options include using accepted statistical methods (eg, use of complete data only, use of multiple imputation, and use of modified weights and model-based procedures). Sensitivity analyses will be conducted using different assumptions regarding the mechanism of missingness.

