## Conclusion

4

If the findings from this pilot trial support the feasibility and acceptability of the MT and AT interventions, we anticipate conducting a fully powered RCT to examine whether MT only, AT only, and MT + AT result in meaningful improvements in cognitive function among patients at high-risk for dementia. Preliminary findings from our exploratory mediation analyses will be used to develop a theoretical framework explaining the mechanisms through which AT and MT, might exert their effect on cognitive function. This framework, along with feedback provided by participants, will be used to design the structure, timing, and delivery of the interventions and assessments used in the larger RCT. Findings that combined AT and MT training is effective in improving cognitive function in individuals at risk of dementia could have enormous impact on the prevention of dementia and age-related cognitive decline.

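### The mediation target is stated as change on change, but the b path is defined on the 3-month mediator without its own baseline, so stable differences between people can show up as a b path.

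*Protocol article*

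**What the plan says.** All references are to the protocol article.

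- **Aim (Statistical analyses).** The exploratory mediation analysis is to assess "associations between changes in fitness and other mediators at 3 months with changes in cognitive score at 6 months". Both sides are changes.
- **Paths (same section, next sentence).** The *a* path is given as "path (group effects on mediators at 3 months"), and the *b* "path (mediators at 3 months on ZAVEN scores at 6 months), using a similar set of mixed effects models as described previously". Neither path mentions change or a baseline mediator.
- **The models referred back to.** Effects on ZAVEN at 3 and 6 months are "estimated using a series of mixed effects longitudinal models controlling for baseline". The random effect in these models, and the reason for it, are given in the sentence that follows: "Models will include a subject-specific intercept to adjust for repeated measures of the outcome over time within participant".
- **Data available (Study assessments).** "Assessments are performed at baseline, intervention completion (3 months), and 6 months since baseline". The abstract lists the mediators among the measures taken at all three visits.
- **Size and use.** "Our choice of sample size (n = 40, 10 participants per condition) was determined by the scope and timeline of this project". The Conclusion says: "Preliminary findings from our exploratory mediation analyses will be used to develop a theoretical framework", which is to help design the larger trial.

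**The concern.** The two sentences describe different regressions. The first relates movement in the mediator to movement in cognition. The second relates where a person stands on the mediator at 3 months to where that person stands on ZAVEN at 6 months.

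On the outcome side, controlling for baseline ZAVEN brings the two close together. On the mediator side nothing does so, because the baseline control in the earlier models concerns the outcome and the mediator enters the b path as a predictor. A 3-month mediator value largely carries over from baseline, and the mediator is not randomized. Baseline ZAVEN is an imperfect measure of underlying cognition, so adjusting for it leaves part of any long-standing link between mediator and cognition in the b coefficient.

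The output of this analysis is an effect size with its interval. A b path that reflects entry differences would favour mediators that merely accompany good cognition, and it would pass into the framework for the next trial.

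A second, separate point is that the subject-specific intercept is justified by repeated outcomes, yet each path as defined has one outcome per person.

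**Working it through.** The article gives no mediation figure to reproduce. Its only related number, 4 × 10 = 40, is consistent.

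**Inputs.** From the article: n = 40, four groups, visits at 0, 3 and 6 months. Assumed, because the article gives no values: correlation ρ between mediator and underlying cognition 0.3 to 0.5; mediator stability s = 0.8; ZAVEN reliability r = 0.7 to 0.8; true b = 0; all variables scaled to SD 1 within group.

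**Step 1: b path with the 3-month mediator, baseline ZAVEN and group.** Let c be the correlation of the 3-month mediator with ZAVEN. Under the null it is the same at baseline and at 6 months. The large-sample coefficient is

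b = c(1 − r) / (1 − c²).

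- Upper end (mediator is a stable trait measured with noise, ρ = 0.5, r = 0.7): c = 0.5 × √(0.8 × 0.7) = 0.374; b = 0.374 × 0.3 / (1 − 0.140) = 0.13.
- Central case (autoregressive mediator, ρ = 0.4, r = 0.7): c = 0.8 × 0.4 × √0.7 = 0.268; b = 0.268 × 0.3 / (1 − 0.072) = 0.087.
- Lower end (autoregressive, ρ = 0.3, r = 0.8): c = 0.8 × 0.3 × √0.8 = 0.215; b = 0.215 × 0.2 / (1 − 0.046) = 0.045.

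The bias is zero only if r = 1 or c = 0, and n does not enter the formula. Simulation at n = 40 agrees: mean b about 0.04 to 0.13, with the 95% interval excluding zero in about 7% to 17% of trials.

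**Step 2: add the baseline mediator.**

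- Autoregressive mediator: given its baseline, the 3-month value holds no further information on cognition, so b = 0.
- Stable trait measured with noise: b = c(1 − r) / (1 + s − 2c²). For ρ = 0.5, r = 0.7: 0.112 / (1.8 − 0.280) = 0.07. For ρ = 0.3, r = 0.8: c = 0.24 and b = 0.048 / (1.8 − 0.115) = 0.03.

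Simulated exclusion of zero is about 4% to 6%.

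**Step 3: wider check.** Trait-plus-noise mediator, the same reliability for mediator and ZAVEN, group in every model, n = 40, 3,000 replicates. Entries are mean b and the share of intervals excluding zero.

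| ρ, reliability | 3-month mediator + baseline ZAVEN | + baseline mediator | change on change |
|---|---|---|---|
| 0.3, 0.6 | 0.074, 7.4% | 0.045, 5.4% | −0.001, 5.1% |
| 0.3, 0.8 | 0.049, 7.2% | 0.026, 5.6% | −0.001, 5.6% |
| 0.5, 0.6 | 0.130, 14.3% | 0.078, 7.3% | −0.005, 4.3% |
| 0.5, 0.8 | 0.100, 14.1% | 0.055, 6.1% | −0.002, 5.3% |

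Runs at n = 4,000 gave nearly the same means, as Step 1 predicts.

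**Step 4: price in precision, central case.** Residual variance of 6-month ZAVEN given baseline ZAVEN is about 1 − 0.7² = 0.51. Without the baseline mediator the model has 6 coefficients, so 34 residual degrees of freedom: SD ≈ √(0.51 / (34 × 0.928)) = 0.13 (simulated values about 0.12 to 0.13). With it, the mediator variance left is 1 − 0.8² = 0.36 on 33 degrees of freedom: SD ≈ √(0.51 / (33 × 0.36)) = 0.21 (simulated about 0.20). Root-mean-square error is √(0.127² + 0.087²) = 0.15 without and about 0.20 with the baseline mediator.

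**Step 5: the intercept.** With one outcome per person, the variance is τ² + σ² (intercept plus residual) and only the sum enters the likelihood. Giving 0%, 30%, 60% or 90% of it to the intercept left the log-likelihood at −49.98 each time. The model is ordinary regression.

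**The case against.** - **Change is shorthand here.** The Secondary outcomes section also speaks of changes from baseline, and the analysis section then models follow-up scores with baseline control. The mediation sentences may follow the same habit, with the parentheses only naming variables and times. This is fair for ZAVEN, and Step 1 already grants it. It does not put the mediator's own baseline into the b path.
- **The covariate rule may cover it.** Variables associated with the outcomes are to be covariates, and a baseline mediator could qualify. But that rule is stated for linear or logistic regression and depends on what is found in the data, so it covers the point only in part.
- **The estimate does not become more accurate.** This stands. Root-mean-square error does not fall with the added covariate. What improves is the centring and coverage of the interval, which matters when the interval is the product.
- **The intercept is harmless.** This also stands. If both ZAVEN visits stayed in one model and only the 6-month term were read off, the intercept would even be identified, but the text does not define the path in that way.

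A reader might infer that the random intercept creates the bias. It does not. A reader might also infer that the two definitions reverse each other's conclusions. Under a null effect, the signs of the two estimates differed in about 40% to 46% of simulated trials, but two unrelated estimates centred on zero would differ in 50%. That is noise around zero and does not show that a real effect would be reversed.

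**Conclusion.** The point holds with minor weight. The text gives two targets for one analysis, and the second lacks the covariate that would make it refer to change. With baseline ZAVEN and group adjusted for, the spurious b is about 0.04 to 0.13, and about 7% to 17% of 95% intervals exclude a true zero. These figures rest on the assumed correlation, stability and reliability and would shrink with a weaker entry correlation or a more reliable composite.

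It would go too far to say that the mediation results will be wrong. The analysis is labelled exploratory, is limited to effect sizes, has no decision rule and touches neither feasibility nor the main cognitive comparison. It still deserves correction, because the Conclusion gives its findings a role in shaping the larger trial. The unidentified intercept is a specification slip with no numerical consequence for b.

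**What to change.** Make both sentences name one target. Then:

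- **b path:** ordinary regression, one row per participant, of 6-month ZAVEN on the 3-month mediator, adjusted for treatment group, that mediator's baseline and baseline ZAVEN. Change on change with group is an acceptable alternative.
- **a path:** ordinary regression of the 3-month mediator on group, adjusted for its baseline.
- **Random intercept:** omit it from both.

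Group must be named in the b path. Without it, a direct effect of the interventions on cognition passes as mediation: with assumed direct effects of 0.5 SD and effects of 0.5 to 0.8 SD on the mediator, mean b is about 0.15 to 0.21 and 10% to 19% of intervals exclude a true zero, even with both baselines in the model.

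The cost is wording, since the baseline mediators are already collected. The price is a wider interval (SD of b about 0.20 in the central case). A residual bias of about 0.03 to 0.07 remains if the mediator is a noisy measure of a stable trait. Change on change removed it in the scenarios run, so reporting both would show how far the result depends on that.

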### Quality control and monitoring

2.9

Quality control measures are implemented across 4 study domains, including treatment fidelity, staff training, data monitoring, and metrics. Assessments of treatment fidelity are performed following the guidelines developed by the Treatment Fidelity Workgroup. Auditor checklists were created during the study start-up period and completed during each MT and AT session to monitor fidelity to the intervention. Optimal treatment fidelity would be evidenced by 100% of objectives met. Staff involved in data collection received training in the administration and scoring of all cognitive measures and questionnaires, as well as how to review assessment instruments immediately for omissions.

For data monitoring, quarterly error-checking procedures have been implemented to ensure that all entered data accurately represent data collected. Additionally, once every 12 months an Independent Study Monitor will review study progress and compile a report detailing adverse events and their likelihood of being related to the study intervention, whether adverse event rates are consistent with prestudy assumptions, rates, and reasons for study withdrawal, whether all participants met entry criteria, and whether continuation of the study is justified. This report is then distributed to the Principal Investigator and the IRB.

### Ethics and dissemination

2.10

Full informed consent and HIPAA authorization is obtained from each participant enrolled into the study. All aspects of the study have received full ethical approval by the IRB at The Miriam Hospital. The IRB will conduct a planned audit of the study every 12 months. Any modifications to the protocol will be submitted as amendments to be reapproved by the IRB. Once approved, the trial registry description (NCT 03289546) will be modified to reflect the changes. Additionally, participants will be reconsented if such modifications include substantive changes to the study procedures or risk/benefit profile. Adverse events experienced by participants are also tracked and reported to the IRB. Given that this is a safe, low-risk pilot behavioral trial, there are no planned interim analyses nor preestablished stopping guidelines.

Results from the Active Minds Study will be disseminated through conference presentations and publication submissions to peer-reviewed journals. An overview of study results will also be posted on the trial registry site at http://www.clinicaltrials.gov. Data generated under the project will be shared as per the NIH Grant Policy and The Miriam Hospital IRB guidelines. After the main findings from the study are accepted for publication, interested researchers may request access to the deidentified data and statistical code for educational and research purposes. All requests will be reviewed by the study Principal Investigator and a data sharing agreement must be finalized between all parties prior to releasing the data.

## Discussion

3

Increasing attention is being devoted to preventive strategies to reduce the occurrence of age-related cognitive impairment and dementia. Early observational findings suggested that interventions that improve cognitive skills may be beneficial. Such evidence has spurred a boom in mass-market cognitive “brain training” apps. Although these approaches are becoming increasingly popular, improvements are apparently limited to task-specific domains and do not transfer to other cognitive skills. What has been shown to be effective, instead, is aerobic exercise, with several RCTs documenting the effect of AT on improved cognition in individuals with mild cognitive impairment or dementia.^[18–21]^ Despite the well-established benefit of AT and the promise of cognitive training, only 4 studies examined the combined effects of these 2 approaches in patients with cognitive impairment. Overall, results from these studies suggest that combining AT with cognitive training may be beneficial.^[22–25]^

Parallel to this work, studies have attempted to determine whether mindfulness-based interventions may lead to improvements in cognitive function. MT has shown improvements in cognitive skills (ie, attention, working memory, and executive function) in both healthy younger and older adults.^[28–33]^ To the best of our knowledge though, MT has never been used to improve cognitive function among individuals at risk for dementia. Among mind-body approaches, tai chi, a Chinese martial art combining slow, gentle body movements, and meditative practices, has shown great promise for reducing risk of dementia among older adults,^[61]^ but because tai chi incorporates both physical activity and meditative practices, it is difficult to identify the “active ingredient(s)” responsible for such improvements and it remains unclear whether improvements in cognition are the result of changes in attention and concentration skills from MT, vascular changes from increased physical activity, or a combination of the 2.

In light of this empirical evidence, this pilot study seeks to explore the possible synergistic effects of aerobic exercise and MT on cognitive function. This study is novel in that these interventions will be applied to a clinically relevant population, that is, individuals at risk for developing dementia.

### Strengths and limitations

3.1

This is the first study to investigate the effects of AT, MT, and their combination in older adults at risk for dementia. By utilizing a 2 × 2 factorial design, we will be able to describe the role of AT and MT on cognitive function and to determine if the combination may produce effects greater than either intervention alone.

Many prior studies examining the effects of AT and mindfulness-based approaches on cognition, used singular outcome measures such as the Mini-Mental State Examination to describe overall, global cognitive functioning. Although less demanding on researchers and participants, such an approach precludes a more nuanced understanding of the effect on different aspects of cognition. For this study we chose to administer a battery of measures to assess cognitive function across several domains. This comprehensive approach will help explore whether the posited benefits of AT, MT, and MT + AT are domain-specific or extend across domains. Last, this study is also strengthened by rigorous assessments of treatment fidelity throughout delivery of the interventions.

We acknowledge that the interventions proposed in this study are both time and labor-intensive. Participants are asked to contribute between 3 and 4 hours per week over the course of 8 to 12 weeks, not including travel time or time taken to complete study assessments. This schedule was chosen to ensure that participants receive a strong enough “dose” of each intervention and to be as consistent as possible with the structure of the MBSR program.

Detailed feedback will be obtained from participants regarding the length, structure, and quality of all aspects of the MT and AT interventions, and their input will be carefully considered in determining the format of the interventions that will be used in future studies. One possible modification could be to deliver MT using a mobile app instead of requiring participation in class-based sessions, which has the potential to significantly reduce participant burden. Another limitation is the small sample size of this study, as such, results will be only preliminary, and will be used to inform a larger RCT designed to establish the efficacy of this approach.

## Conclusion

4

If the findings from this pilot trial support the feasibility and acceptability of the MT and AT interventions, we anticipate conducting a fully powered RCT to examine whether MT only, AT only, and MT + AT result in meaningful improvements in cognitive function among patients at high-risk for dementia. Preliminary findings from our exploratory mediation analyses will be used to develop a theoretical framework explaining the mechanisms through which AT and MT, might exert their effect on cognitive function. This framework, along with feedback provided by participants, will be used to design the structure, timing, and delivery of the interventions and assessments used in the larger RCT. Findings that combined AT and MT training is effective in improving cognitive function in individuals at risk of dementia could have enormous impact on the prevention of dementia and age-related cognitive decline.
